**Primary outcomes include**

Leisure-time Physical Activity. Participants' leisure-time moderated-to-rigorous physical activity will be assessed by using the Fitbit Orb (San Francisco, IL) which is a wearable, display, triaxial accelerometer that pairs with Bluetooth with compatible smartphones. It can monitor the heartbeat rate of users for each minute. Participants will be asked to wear the Fitbit tracker for more than 10 hours a day (defined as daily adherence) throughout the study period. This accelerometer-based wristband activity tracker has shown its validity in measuring physical activity in cohorts with SCI [26].

Depression. The 9-item Patient Health Questionnaire will be used to measure the participants' depression level. Participants will be asked to rate "how often they were bothered by specific symptoms over the last two weeks" with each item rating from 0 (not at all) to 3 (nearly every day). Higher scores indicate greater symptoms of depression. The scale has indicated satisfactory reliability in the SCI population [16].

Chronic Pain. An 11-point numerical pain rating scale will be used to access pain intensity (in the past week), where zero means no pain and 10 means the worst imaginable pain. The scale has demonstrated good reliability in the Chinese SCI population [20].

**Secondary outcomes include:**

Exercise Efficacy. The 10-item Chinese version of the self-efficacy for exercise will be used to evaluate participants' confidence level (from 0 not confident to 10 very confident) regarding engaging in regular exercise. The average scores of ten items will be calculated, with the higher scores indicating greater exercise efficacy. The scale demonstrated good reliability and validity in Chinese people using wheelchairs [27].

Mindfulness. The 39-item Five Facet Mindfulness Questionnaire will be used to measure the five aspects of mindfulness including observing, describing, acting with awareness, non-judgmental and non-reactive. Answering on a five-point Likert scale (from 1 never to 5 always true), higher scores denote greater levels of mindfulness. Satisfactory reliability was found for each subscale in the SCI population [28].

Quality of life. The 26-item World Health Organization Quality of Life Brief Scale will be used for assessing participants' quality of life in four domains including physical health, psychological health, social relationships, and environment. Higher scores indicate greater perceived quality of life with grading on a five-point Likert scale. This scale has demonstrated strong psychometric characteristics of good reliability in the SCI population [28].

#### Data collection and processing

With participants' written consent, pre-intervention test will be conducted face-to-face (or online if participants cannot come to the study site) by filling out the questionnaires by the participants by participants on their own. Assistance for those who have difficulties in filling out surveys will be provided by their caregivers or research assistants. At post-intervention and 3-month follow-up, the research assistant will use the same set of outcome questionnaires but the evaluation will be online. Focus groups will be conducted online as described above in the 'feasibility and acceptability' section. With their consent, the interviews (and intervention sessions) will be audio-taped for content analysis.

## Data analysis

All quantitative data from the pre- and post-tests will be numerically coded, summarized (with descriptive statistics), and analyzed using IBM SPSS 26. Both intention-to-treat and per-protocol analyses will be performed. Effect sizes of between-group comparisons will be estimated using Cohen's *d* which is applicable for small sample sizes [29]. Comparison of baseline information between two study groups will be performed by t-test, Mann-Whitney U, and/or Chi-square tests depending on the nature of the data. The generalized estimating equation will be used to assess the changes in the outcome measurements between groups over time, followed by contrast tests. Co-variance (if any found in the baseline comparison) will be adjusted during the analysis of intervention effects. Subgroup analysis will be conducted for certain factors (e.g., complete and incomplete injury or intervention completion and non-completion). Level of significance is set at  $p < 0.05$  (2-tailed).

Focus group interview data will be content analyzed. Tape-recorded interviews will be transcribed into Cantonese by one research assistant and cross-checked by the other research assistant. Codes will be discussed and agreed between our team members, combined to form categories/subcategories, and explained with verbatim data. Any discrepancy in coding/category will be discussed and final themes/subthemes will be confirmed by our team.

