#### Sample size

As this proposed study is to develop and evaluate the feasibility, acceptability, and preliminary effectiveness of the PPI intervention, a widely acceptable sample size (i.e., 30 participants in each study group) for a preliminary analysis to examine intervention feasibility and to estimate a between-group effect will be adopted [22]. Considering a 20% attrition rate, 36 people with SCI per study group (i.e., 72 people in total) will be recruited. A purposive sampling by key informants (containing both participants who completed the whole intervention sessions and those who withdrew from the intervention period) will be conducted for focus-group interviews (i.e., 4-5 participants per group), until saturation of the information was reached.

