#### Randomization and masking

After the completion of the baseline assessment, eligible participants will be randomly allocated to two study groups. The random allocation will be conducted by an independent researcher with an external randomization service (i.e., sealedenvelope.com), using random permuted block sizes (i.e., 4 or 6) to ensure balanced group numbers. Participants will not be blinded due to the nature of the intervention. Participants will be reminded to keep the intervention content confidential and not discuss this with participants in the control group to avoid contamination. Assessor-blind is not adopted as measurements are self-reported. Assistance provided by caregivers and research assistants might be needed for those who have difficulties in filling out surveys.

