employment, marital status, ethnicity, cause, level of injury, and time since the injury. The following outcomes/instruments will be used to assess the preliminary effects of the PPI intervention. Effect sizes (e.g., Cohen's d) and confidential intervals will be calculated to estimate the sample size for a future fully powered randomized controlled trial.

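### Minor: Cohen's d is justified by its suitability for small samples, but uncorrected d is biased away from zero there; Hedges' g is the corrected form

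*Protocol*

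**What the plan says.** Under (iv) Data processing and analysis, the Data analysis section of the protocol names Cohen's d as the measure for between-group comparisons and gives a reason, with a citation: it is a statistic "which is applicable for small sample sizes".

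The Preliminary effectiveness section gives the values a purpose. Effect sizes (Cohen's d is given as an example) and intervals "will be calculated to estimate the sample size for a future fully powered randomized controlled trial".

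The Sample size section adopts "a widely acceptable sample size (i.e., 30 participants in each study group"), and then: "Considering a 20% attrition rate, 36 people with SCI per study group (i.e., 72 people in total) will be recruited".

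The Data analysis section also plans a per-protocol analysis and subgroup analyses: "Subgroup analysis will be conducted for certain factors (e.g., complete and incomplete injury or intervention completion and non-completion"). It gives no sizes for these sets and does not say whether d will be computed in them. Neither section says whether d will be corrected for small samples.

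**The concern.** Cohen's d divides the mean difference by an estimated pooled SD. Because the SD is estimated, the expected value of d lies further from zero than the true standardised difference, and the gap widens as the degrees of freedom fall. Small-sample suitability is therefore a reason to prefer Hedges' g, which is d multiplied by a correction factor, over plain d.

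This is something the protocol states, not a detail it leaves open. It names a statistic and gives it a rationale, and a later author could take that rationale to mean that small-sample bias is already dealt with. What is at stake is the handover to the main trial. Required sample size varies with 1/d², so an effect size inflated away from zero yields a trial that is somewhat too small for the true effect.

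**Working it through.** **Inputs from the protocol**
- 30 evaluable per group, 20% attrition, 36 recruited per group (Sample size).
- 1:1 allocation, implied by equal groups and by "using random permuted block sizes (i.e., 4 or 6) to ensure balanced group numbers" (Randomization and masking).
- Two-sided 5% significance level (Data analysis).

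**Assumed, because the protocol gives no figure**
- True standardised effect δ of 0.3, 0.5 or 0.8.
- Main-trial power of 80%.
- An illustrative subset of 15 per arm.

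**Step 1: the plan's own figure.** 30 × 1.20 = 36 per group, 72 in total, as stated. If 20% of the 36 are lost, 36 × 0.80 = 28.8, about 29 per group. The analysed number per arm therefore lies between about 29 and 36.

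**Step 2: bias of d.** With df = 2n − 2, the exact correction factor is

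J = Γ(df/2) / [√(df/2) · Γ((df − 1)/2)].

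The expected value of d is δ/J, and g = J × d. The inflation is 1/J − 1. Since required n varies with 1/d², the shortfall in main-trial n is about 1 − J².

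| n per arm | df | J | Inflation of d | Mean d if δ = 0.5 | Shortfall in main-trial n |
|---|---|---|---|---|---|
| 36 | 70 | 0.9892 | 1.1% | 0.505 | 2.1% |
| 30 | 58 | 0.9870 | 1.3% | 0.507 | 2.6% |
| 29 | 56 | 0.9865 | 1.4% | 0.507 | 2.7% |
| 15 (assumed subset) | 28 | 0.9729 | 2.8% | 0.514 | 5.3% |

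A simulation of 200,000 trials agrees: with δ = 0.5 the mean d was 0.507 at 30 per arm and 0.514 at 15 per arm.

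**Step 3: effect on the main trial.** Participants per arm for a two-sample comparison at 80% power, two-sided 5%:

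| δ | n from δ | n from mean d, pilot of 30 per arm | Power at δ with that n | n from mean d, pilot of 36 per arm |
|---|---|---|---|---|
| 0.3 | 175 | 170 | 79.0% | 171 |
| 0.5 | 63 | 62 | 79.5% | 62 |
| 0.8 | 25 | 24 | 79.1% | 25 |

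**Step 4: set against sampling error.** For δ = 0.5, SE(d) ≈ √(2/n + δ²/(4n)).
- 36 per arm: SE 0.239, so the 95% half-width is 1.96 × 0.239 ≈ 0.47.
- 30 per arm: SE 0.262, half-width 0.51.
- 29 per arm: SE 0.267, half-width 0.52.

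At 30 per arm the bias of about 0.0066 is 0.0066/0.262 ≈ 0.025 of a standard error. At 15 per arm the half-width is 0.73 against a bias of about 0.014.

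**The case against.** The strongest reply is that this does not matter at the planned size. A bias of about 1% is lost in an interval roughly one unit wide, and the protocol plans intervals alongside the effect sizes. At 30 per arm with a true effect of 0.5, the pilot d falls below the truth 49.7% of the time and its median is 0.502, so an individual estimate is almost as likely to be too low as too high. All of that stands, and it is why the point is minor.

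A second reply is that the protocol does not rule out a correction: Preliminary effectiveness offers Cohen's d only as an example, and an analysis plan may specify one. That is fair as far as it goes. But Data analysis names d without qualification and defends it on small-sample grounds, so the rationale is still wrong as written.

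Three stronger readings are tempting, and the protocol does not support them:
- **That the error always favours the intervention.** The bias is multiplicative and away from zero. It vanishes when there is no effect and makes a harmful effect look more harmful.
- **That subgroup effect sizes are materially overstated and carried into the main trial.** The protocol gives no subgroup sizes, does not say that d is computed within subgroups, and does not say that such values size the next trial.
- **That the choice of SD inflates d.** Under equal variances, using the change-score SD instead of the baseline SD multiplies d by 1/√(2(1 − r)), where r is the pre-post correlation. That is 1.29 at r = 0.7 but 0.85 at r = 0.3 and 0.79 at r = 0.2. The direction depends on a correlation the protocol does not give, and the choice of SD is ordinary analysis-plan detail.

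**Conclusion.** The point holds as a minor correction. The protocol gives small-sample suitability as its reason for Cohen's d, whereas uncorrected d is biased away from zero in small samples, and the values are meant to inform the size of a later trial.

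At 29 to 36 per arm the inflation is about 1.1% to 1.4% and the main-trial n about 2% to 3% too low. The cost is at most about one percentage point of power. These figures assume that d is left uncorrected, that data are normal with equal variances, that arms are equal, and that the main trial is sized directly from the pilot point estimate. The counts per arm also rest on the assumed effects of 0.3 to 0.8 and 80% power.

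Inflation would be larger in any smaller set for which d is computed. The figure of about 3% at 15 per arm only illustrates this and is not a planned size.

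It would be wrong to conclude that this bias is what makes the pilot a weak basis for sizing a trial. Imprecision dominates, with a half-width of about 0.5, and Hedges' g does not reduce that appreciably.

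**What to change.** In Data analysis, delete the small-sample rationale and replace Cohen's d with Hedges' g. Make the same replacement where Cohen's d is the example in Preliminary effectiveness. Suggested wording: between-group effect sizes will be reported as Hedges' g (standardised mean difference with small-sample correction) with 95% confidence intervals. If effect sizes are reported for the per-protocol set or any subgroup, use the same statistic there.

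The cost is one wording change and a one-line calculation (g = J × d). Data collection, sample size and the planned model are unaffected. The only downside is that reported effect sizes become about 1% smaller at the planned size.

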### (iii) Interventions

The Intervention Group--The eight-week Physical-Psychological Integrative online-group intervention

Part I: Physical exercise. A guiding video of performing exercises was specifically developed for the SCI population by two experienced physiotherapists in Hong Kong. The video mainly includes warm-up, mobilization, strength exercises, aerobic exercises, and cool-down sessions.

Part II: An eight-week online intervention. The PPI intervention includes eight weekly online groups (with 4-5 participants in a group) sessions (with each session lasting for 60-90 minutes). At the beginning of each online group meeting, the intervention provider will use motivational interviewing techniques [23] to promote participants' adherence to the physical activity program mentioned in Part I, followed by online group psychological intervention. The content of the intervention will be adapted from the mindfulness-based stress reduction proposed by Kabat Zinn (1992), practice guideline of 'mindfulness for health' to relieve pain, reduce stress, and restore well-being [24]. The content of the intervention includes eight themes/sessions (the details of the intervention content are shown in Appendix 2): Session 1- Orientation and engagement; Session 2- Awareness and Acceptance; Session 3- Non-judgement; Session 4- Stay present and let go; Session 5- Our thoughts are not real & Response without reacting; Session 6- Empowerment of self-management and discuss pain management; Session 7- Seek out pleasant things and social support; Session 8- Review the intervention and end the programme. Two audio-tape recorded sessions (i.e., 20 minutes each) of mindfulness practice will be given to the participants for their daily practice. The intervention will be carried out by an experienced social worker trained in psychology, motivational interviewing, and mindfulness-based stress reduction.

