### The control group

Participants in the control group will receive a video call (approximately 60 minutes each week for eight weeks) from the trained research assistant with psychological background, i.e., to provide general physical and psychological suggestions (e.g., encouragement of performing physical activities, and communication skills with family members/friends, and engagement in the community life). This is to control the contact effects of the PPI intervention.

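### The protocol makes no allowance for clustering by therapy group in the PPI arm, so standard errors will be somewhat too small if outcomes correlate within groups

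*Protocol*

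**What the plan says.** Protocol, Randomization and masking: individuals are the unit of allocation ("eligible participants will be randomly allocated to two study groups").

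Protocol, (iii) Interventions: PPI consists of "eight weekly online groups (with 4-5 participants in a group) sessions". One provider role is named: "The intervention will be carried out by an experienced social worker trained in psychology, motivational interviewing, and mindfulness-based stress reduction". Interaction between members is an intended ingredient. Session 7 includes social support, and Appendix 2 has sessions that discuss participants' problems and a last session that aims at networks among peers.

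Protocol, The control group, on how contact is delivered: "Participants in the control group will receive a video call (approximately 60 minutes each week for eight weeks) from the trained research assistant". No groups are mentioned.

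Protocol, Data analysis: "The generalized estimating equation will be used to assess the changes in the outcome measurements between groups over time, followed by contrast tests". The only adjustment named is this: "Co-variance (if any found in the baseline comparison) will be adjusted during the analysis of intervention effects". Tests are two-sided at 0.05. Neither this section nor Sample size mentions therapy group, ICC or design effect.

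**The concern.** Participants are randomised one by one, but those in the PPI arm then spend eight weeks in small groups. After baseline, their outcomes may resemble those of their own group more than those of other PPI participants. The control arm has no matching structure on the page. This is a partially nested design, with clustering in one arm only.

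A GEE that takes the participant as its cluster handles the correlation between one person's visits and assumes that different people are independent. With positive correlation within therapy groups, the PPI mean varies more than that model reports. Intervals are then too narrow and p-values too small.

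This matters even in a pilot, for two reasons. The hypotheses are framed as significantly greater improvement. The effect sizes and intervals are also meant to size the main trial, and a main trial of a group intervention needs some idea of the ICC, which the protocol does not plan to estimate.

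**Working it through.** **Inputs from the protocol.** 30 evaluable and 36 recruited per arm, 20% attrition (Sample size); groups of m = 4 to 5 (Interventions); two-sided alpha 0.05 (Data analysis).

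**The plan's own figure.** 30 × 1.2 = 36 per arm, 72 in total, as stated. At 20% loss, 36 × 0.8 = 28.8 remain per arm. There is no power calculation to reproduce.

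**Number of groups.** 36 / 5 = 7.2, so at least 8; 36 / 4 = 9. Hence 8 or 9 groups.

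**Assumption.** The documents give no ICC. I take 0.05, 0.10 and 0.20, with 0 as reference.

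**Formulas**
- Design effect in the PPI arm: DE = 1 + (m − 1) × ICC.
- True over reported SE of the arm difference, equal arms, no clustering in controls: f = √((1 + DE) / 2).
- Actual two-sided error at nominal 5%: 2 × (1 − Φ(1.96 / f)).
- 95% half-width for a standardised difference, 30 per arm: 1.96 × √(2/30) × f = 0.506 × f.
- Effective PPI sample size out of 30: 30 / DE.

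Example, m = 5 and ICC 0.10: DE = 1 + 4 × 0.10 = 1.40; f = √(2.40 / 2) = 1.095; half-width = 0.506 × 1.095 = 0.554.

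| ICC | DE (m = 4 to 5) | f | Actual error | Half-width for d | Effective PPI n of 30 |
|---|---|---|---|---|---|
| 0 | 1.00 | 1.00 | 5.0% | 0.506 | 30 |
| 0.05 | 1.15-1.20 | 1.037-1.049 | 5.9-6.2% | 0.525-0.531 | 25-26 |
| 0.10 | 1.30-1.40 | 1.07-1.095 | 6.8-7.4% | 0.543-0.554 | 21-23 |
| 0.20 | 1.60-1.80 | 1.14-1.18 | 8.6-9.8% | 0.577-0.599 | 17-19 |

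**The planned contrast.** The table compares scores at one visit. The GEE compares changes over time, and there the effect is larger: subtracting baseline removes variance between persons but leaves the group effect that arises after baseline. With an assumed within-person correlation of 0.6, a change score has variance 2 × (1 − 0.6) = 0.8. An ICC of 0.20 on the score is therefore 0.20 / 0.8 = 0.25 on the change. With m = 4.5, DE = 1 + 3.5 × 0.25 = 1.875 and f = √(2.875 / 2) = 1.20, against 1.16 on the score.

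**Simulation of that contrast.** Null trials, participant-level robust SE without small-sample correction, within-person correlation 0.6, eight PPI groups, with either 36 per arm or groups thinned by attrition to 29 per arm. Type I error was:
- about 5.8% at ICC 0, which is small-sample bias of the robust SE and not clustering;
- about 7% at ICC 0.05;
- about 8% at ICC 0.10;
- about 10-11% at ICC 0.20.

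These are rounded; runs and layouts differ by a few tenths of a percentage point.

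**The case against.** **The cluster level is not stated.** A reader might infer that the plan treats all participants as independent. The protocol does not say so. It names a GEE and leaves open the clustering unit, the working correlation and the variance estimator. A GEE can take therapy group as its cluster, and a SAP that is not shown may settle this. That stands, and it is why the point is conditional. It does not remove the point: the protocol fixes both the delivery in groups and the type of model, and the only dependence it names is over time. Nor would clustering on therapy group settle matters by itself, because with 8 or 9 PPI groups an uncorrected robust SE is unreliable.

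**The control may not be one-to-one.** The words are "Participants in the control group will receive a video call". Individual calls are implied, not stated. If controls also met in groups, that arm would need the same treatment.

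**The intervals may not be too narrow at all.** A reader might infer that every interval is too narrow. That requires a positive ICC, which the documents do not give.

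**The effect is modest.** At ICC 0.05 the half-width for d moves only from 0.506 to 0.525-0.531, and the estimate of d is barely affected. If dropout thins eight groups evenly, m falls to 36 × 0.8 / 8 = 3.6 and f to 1.03, 1.06 and 1.12 at ICC 0.05, 0.10 and 0.20. This is fair, and the point should not be pressed as a threat to a pilot whose first purpose is feasibility.

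**Larger error rates should not be quoted as typical.** Six full groups with 29 per arm gives about 12-13% at ICC 0.20. That layout supposes that whole groups leave, and the figure also contains the small-sample bias seen at ICC 0.

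**Conclusion.** The concern holds in conditional form. The protocol creates therapy groups in one arm and names no allowance for them in the analysis. If the GEE clusters on the participant only, and outcomes correlate within groups, the precision of the post-intervention and 3-month contrasts is overstated. The true SE is then 4-5% larger than reported at ICC 0.05 and 14-18% larger at ICC 0.20. The change-contrast error is about 7% to 10-11%, against about 5.8% without clustering.

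This rests on an assumed ICC, on groups of 4-5, on controls without clustering and, for the error rates, on a within-person correlation of 0.6. At ICC 0 nothing is lost to clustering. The change is worth making because it is cheap and because the pilot is meant to inform a larger trial.

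**What to change.** Record each PPI participant's therapy-group ID when groups are formed. State in the protocol or SAP that the outcome model accounts for it, by one of two routes:

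- a partially nested linear mixed model: repeated measures within person, a random therapy-group effect in the PPI arm only, each control as a singleton, and Satterthwaite or Kenward-Roger degrees of freedom; or
- the planned GEE with therapy group as the cluster in the PPI arm, each control as a singleton, and a small-sample variance correction.

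State also whether control calls are individual, and confirm that the software named in the protocol offers the chosen correction. Report the ICC with its confidence interval as a rough input to main-trial planning.

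The cost is one ID variable and a changed model statement. Intervals become slightly wider, and an ICC from about 8 groups will be imprecise. The change does not separate the effect of the single PPI provider from the effect of the arm; that confounding remains and should be acknowledged.

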### Ethical considerations

Ethical approval will be obtained from the Hong Kong Polytechnic University. This study will be performed in accordance with the Helsinki Declaration. Written informed consent will be obtained from all participants before the baseline assessments of the study, and will also be obtained from purposely sampled participants prior to all focus-group interviews. Participation is entirely voluntary for people with SCI and they can withdraw from the research at any time without any penalty. Participants' identities and data (information

collected and videotape records) will be protected by maintaining anonymity and confidentiality. Only authorized personnel can access the data for analysis.

(iv) Data processing and analysis

Feasibility and acceptability

**The feasibility** assessment of subject recruitment and follow-up will include (1) time taken to recruit the target sample size; (2) recruitment rate: the number of eligible participants approached who agree to consent divided by all subjects eligible to participate; (3) retention rate: the number of participants who complete the study divided by all participants who agree to consent; (4) drop-out rate: the number of participants who dropped out after randomization divided by all participants who agree to consent; and (5) reasons for dropping out will be collected from participants who dropped out.

**The acceptability** of the intervention will be indicated by (1) adherence rate: the number of PPI intervention sessions practiced divided by the total number of required sessions; (2) adverse events record associated with PPI intervention; and (3) satisfaction: participants' satisfaction with the intervention will be assessed with the Client Satisfaction Questionnaire [25]. The acceptability of the intervention will also be assessed by focus-group interviews with a purposive sample of participants who completed the whole intervention sessions and those who withdrew from the intervention period. Participants' perspectives about the acceptability, strengths, and limitations of the study and suggestions on the improvements of the interventions will be explored.

Preliminary effectiveness

All participants will be assessed at pre-, post-intervention, and 3-month follow-up by the research assistant. A self-designed form will be used to collect data on participants' socio-demographics and medical history, including age, gender,

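### GEE is the named longitudinal model with 20% attrition expected; a baseline-adjusted likelihood model is safer if dropout depends on earlier scores and differs by arm, and is more precise

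*Protocol*

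**What the plan says.** Under Data analysis the Protocol states: "The generalized estimating equation will be used to assess the changes in the outcome measurements between groups over time", with contrast tests to follow. The same section says "Both intention-to-treat and per-protocol analyses will be performed" and does not tie GEE to either analysis set. Covariates are adjusted for only if the baseline comparison shows a difference, so the baseline value of the outcome is not routinely in the model.

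Under Sample size: "Considering a 20% attrition rate, 36 people with SCI per study group (i.e., 72 people in total) will be recruited". Attrition appears there only as an inflation factor, with no mechanism, timing or difference between arms.

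Under Preliminary effectiveness: "All participants will be assessed at pre-, post-intervention, and 3-month follow-up by the research assistant". That gives three visits. The effect sizes and intervals are meant to inform the sample size of a later, fully powered trial.

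No working correlation, weighting, imputation or missing-data assumption is given. Those details may sit in a SAP that is not shown, and their absence is not the point here. The point is the choice of model, which is stated.

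**The concern.** Without weighting or imputation, GEE estimates are in general consistent only if dropout is unrelated to the outcomes, including those already observed. A likelihood model with a correctly specified covariance needs the weaker condition that dropout depends only on observed data.

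The Protocol makes score-dependent dropout believable, though it does not predict it. The Introduction links more negative emotion and lower self-efficacy to less engagement in activity, and depression is a primary outcome. The arms also differ in what they ask. The intervention has eight group sessions of 60 to 90 minutes plus exercise and daily mindfulness practice; the control arm has a weekly video call of about 60 minutes. Participants are not blinded.

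At stake is the 3-month effect that would size the next trial. A confidence interval reflects sampling error; it does not reflect this bias.

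The second issue is precision. A group-by-time contrast compares change from baseline, which uses the baseline score less efficiently than adjusting for it.

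**Working it through.** **The plan's own figure.** 30 × 1.20 = 36 per group, 72 in total, as stated. The Protocol gives no SD, correlation or dropout model, so it has no bias figure to reproduce.

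**Inputs from the Protocol.** Three visits, two equal arms, 20% attrition, GEE with contrasts.

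**Assumed inputs.** SD 1 and no true effect. Between-visit correlations are 0.5 to 0.7, constant or autoregressive. A further decaying pattern has 0.5 (baseline–post), 0.35 (baseline–3 months) and 0.7 (post–3 months). Dropout depends on an earlier observed score with an odds ratio of 2 or 4 per SD, or deterministically as an extreme.

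**Step 1. Closed form for independence.** With a separate mean for each arm and visit, independence GEE returns the observed 3-month means. If the 20% with the worst post-intervention scores leave, that arm's 3-month mean shifts by ρ × φ(z₀.₈)/0.8 = 0.35ρ, where ρ is the post–3-month correlation.
- ρ = 0.5: 0.175 SD in one arm, 0.35 SD if the arms go in opposite directions.
- ρ = 0.7: 0.245 and 0.49 SD.

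The simulated deterministic values, 0.18–0.26 and 0.35–0.51 SD, agree.

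**Step 2. Large-sample simulation, correlations 0.5 to 0.7.** Absolute bias of the 3-month difference, in SD, at 20% dropout:

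| Dropout pattern | Odds ratio per SD | Independence GEE | Exchangeable GEE | Unstructured GEE | Unstructured likelihood |
|---|---|---|---|---|---|
| Same mechanism and rate in both arms | 2–4 | about 0 | about 0 | about 0 | about 0 |
| Score-dependent in one arm only | 2 | 0.07–0.10 | up to 0.02 | up to 0.01 | within 0.01 |
| Score-dependent in one arm only | 4 | 0.11–0.17 | up to 0.03 | up to 0.04 | within 0.01 |
| Opposite directions | 2 | 0.13–0.19 | up to 0.02 | up to 0.01 | within 0.01 |
| Opposite directions | 4 | 0.21–0.33 | up to 0.03 | up to 0.04 | within 0.01 |

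The exchangeable and unstructured GEE entries are ceilings over all patterns at that odds ratio. With the same direction in both arms but 30% against 10% dropout, independence GEE is biased by 0.06–0.22 SD across all strengths, deterministic included. At the deterministic extreme with opposite directions, exchangeable GEE reaches about 0.09 SD and unstructured GEE about 0.16 SD.

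**Step 3. Decaying pattern 0.5/0.35/0.7, dropout after the post-intervention visit.** An exchangeable structure fits worse here. Its bias is 0.02 SD (one arm, odds ratio 2), 0.04 (one arm, 4), 0.05 (opposite, 2) and 0.09 (opposite, 4). Independence gives 0.09, 0.15, 0.18 and 0.30. The unstructured likelihood model stays within 0.01. The 0.09 in this pattern is the upper end of the exchangeable range quoted in the conclusion.

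**Step 4. Precision with complete data.** The variance of a change score is 2(1 − ρ) and of a baseline-adjusted score 1 − ρ², where ρ is now the correlation with baseline. The ratio is (1 + ρ)/2: 0.75 at ρ = 0.5 and 0.80 at ρ = 0.6, so adjustment lowers the variance by 25% and 20%.

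**Step 5. Scale.** The unadjusted standard error of a difference at 30 per group is √(2/30) = 0.26 SD. As an illustration for the next trial (assumed true d = 0.5, 80% power, two-sided 5%), n per arm ≈ 15.7/d² = 62.8, or 63. An estimate inflated by 0.03 SD gives 15.7/0.53² = 55.9, or 56. Inflated by 0.09 it gives 15.7/0.59² = 45.1, or 46. Deflated by 0.09 it gives 15.7/0.41² = 93.4, or 94.

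**The case against.** **The protocol leaves the details open.** It names no independence structure and excludes neither weighting nor imputation, and these are usual SAP content. That stands. A reader might infer that the plan carries a bias of about 0.3 SD; the documents do not support this. That size needs an independence working correlation together with strong dropout in opposite directions, and neither is stated. Nor is it an upper bound, since the deterministic extreme gives 0.35–0.51 SD.

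**Arm-specific dropout is conjecture.** Controls also have weekly contact for eight weeks, activity trackers are offered as a retention incentive, and reasons for dropout are collected. That stands too: with the same mechanism and rate in both arms the bias is about zero.

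**The gain may come from the covariance, not from likelihood.** This is partly right. With autoregressive data and strong opposite dropout, a random-intercept mixed model was biased by 0.055 SD against 0.066 for exchangeable GEE. The benefit needs an unstructured covariance.

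**GEE with robust errors suits skewed or count outcomes.** The concern is fair for PHQ-9, pain, activity minutes and active days. It does not defeat the change for the continuous outcomes: in simulated trials of 36 per arm with skewed data, the baseline-adjusted likelihood estimate had an SD of 0.23 against 0.28 for exchangeable GEE.

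**Cohen's d is not said to come from the GEE.** Correct, so the bias need not pass into the next sample size. But a d computed from observed 3-month means would carry the bias shown for independence.

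**Conclusion.** The concern holds in a limited form. GEE is a stated choice, attrition is expected, and a better-suited model is available. Under the assumed correlations and odds ratios of 2 to 4 per SD, with score-dependent dropout in one arm or in opposite directions, the bias is about 0–0.09 SD with an exchangeable structure and 0.07–0.33 SD with independence. The precision gain of 20–25% in variance, at correlations of 0.5–0.6, does not depend on dropout.

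Three stronger inferences are not supported. The first is that GEE is designated the intention-to-treat model: both analysis sets are planned and GEE is assigned to neither alone. The second is that GEE is wrong here whatever the dropout. The third is that a mixed model is a free remedy: it relies on missing at random and an adequate covariance, and does not cure dropout that depends on unobserved scores.

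For a 72-person pilot this is worth changing but does not undermine the study. With a non-independence structure and non-extreme dropout, the bias is well below the 0.26 SD standard error.

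**What to change.** For the continuous outcomes, name a likelihood-based repeated-measures model with arm, visit, arm-by-visit and the baseline value. Use an unstructured covariance over the post-intervention and 3-month visits, with Kenward-Roger or Satterthwaite degrees of freedom. Include every randomised participant with at least one post-baseline value. Alternatively, keep baseline as a response with equal arm means, so that all randomised participants contribute; the baseline-as-covariate form cannot use anyone with no later visit.

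Take the post-intervention and 3-month effect estimates and intervals for the future sample size from this model. If GEE is kept, for example for active-day counts, run it on multiply imputed data with a non-independence working correlation.

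The cost is a change of analysis wording and no new data. Residual checks are needed for skewed outcomes, and the missing-at-random assumption should be stated.
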